## Abstract

**Background:**

Substance use disorder (SUD) affects over 20 million adults and costs over $700 billion annually in the United States. It is one the greatest health care challenges we face.

**Objective:**

This research project seeks to enhance the standard practice of Screening, Brief Intervention, and Referral to Treatment (SBIRT) through a mobile solution easily incorporated into primary care that will promote shared decision making and increase referral and adherence to specialty care through continued follow-up care.

**Methods:**

This research will conduct an Office of Management and Budget (OMB)–approved randomized controlled trial (RCT) in primary care and SUD specialty service providers. The RCT will recruit a total of 500 SUD patients. Recruited patients will be randomized into control and intervention arms. Both arms will take initial baseline and exit (30 days) surveys to evaluate self-reported substance use and specialty service utilization. The control arm patients will receive usual care. The intervention group patients will receive technology-enhanced SBIRT and a mobile follow-up program to track goals and substance use at home. The RCT tracks participants for 30 days after the primary care encounter. We will collect feedback from the patients during the 30 days and count the number of patients who use specialty care services in specialty care programs for tobacco, alcohol, and drug abuse (both from self-reporting and from the service providers).

**Results:**

RCT and data collection are underway. We expect to report the data results in 2018.

**Conclusions:**

We expect that significantly more intervention group patients will receive specialty SUD care within 30 days following the SBIRT encounter at the primary care clinic compared to the control group. We also expect that the intervention group patients will report a greater reduction in substance use and a greater drop in Drug Abuse Screening Test and Addition Severity Index scores within 30 days.

## Introduction

### Background

Substance abuse is a serious public health concern in the United States, with severe medical, legal, and economic consequences. In 2012, an estimated 23.9 million Americans aged 12 years or older had used an illicit drug or abused a psychotherapeutic medication (such as a pain reliever, stimulant, or tranquilizer) in the past month, and 17.7 million Americans were dependent on or abused alcohol [1]. Recently, there has been a dramatic increase in the misuse of prescription medications, with emergency department visits involving their abuse increasing by 98.4% between 2004 and 2009 and associated increases in overdose deaths [2]. Abuse of alcohol and illicit drugs is costly, with over $30 billion in health care–related costs for alcohol abuse and $11 billion for illicit drugs [3]. Unfortunately, few needing treatment for drug or alcohol abuse get the treatment they need in a timely manner. According to the Substance Abuse and Mental Health Services Administration’s National Survey on Drug Use and Health, 23.5 million people aged 12 years or older needed treatment for an illicit drug or alcohol abuse problem in 2009, but of these, only 2.6 million received treatment at a specialty facility [4].

### Substance Abuse Screening and Treatment in Primary Care

The health care landscape for patients with substance use disorders (SUDs) is changing. Recently, there has been a push to incorporate mental and behavioral health treatment into primary care, including screening and treatment for alcohol and drug dependence. The Patient Protection and Affordable Care Act, for example, designates mental health and substance use disorders as essential health benefits to be covered by health insurance plans [5]. The US Preventive Services Task Force (USPSTF) recommends screening for alcohol misuse for adults aged 18 years and older and has found sufficient evidence to suggest that brief behavioral counseling interventions in the primary care setting are effective in reducing heavy drinking episodes in adults engaging in risky drinking behaviors [6]. However, the USPSTF has not found sufficient evidence to assess whether screening for illicit drug use in the primary care setting is beneficial, primarily because the majority of studies have focused on patients already exhibiting clear symptoms of drug abuse [7]. Nevertheless, drug-specific pharmacotherapy and behavioral interventions such as brief motivational counseling for illicit drug use have been proven effective in the short-term [7], and the Centers for Medicare and Medicaid Services provides reimbursement to providers who implement the Substance Abuse and Mental Health Services Administration Screening, Brief Intervention, and Referral to Treatment (SBIRT) model in their practices [8]. The SBIRT model is an evidence-based practice designed to identify, reduce, and prevent problematic use, abuse, and dependence on alcohol and illicit drugs and can be incorporated into a primary care practice with the addition of screening questions into the health history questionnaire and training for health care providers to review the responses and identify high-risk patients.

The implementation of screening and intervention for substance use disorders, such as SBIRT, in the primary care setting has faced several challenges. In the past, physicians have cited barriers such as lack of time, lack of access to treatment, and lack of financial resources—both patient financial issues and reimbursement for the physician from health insurers [9]. The new health care changes will do a great deal in easing some of the cost-related barriers; however, physicians and other health care providers still experience barriers to screening and intervention for SUDs such as lack of time, lack of training, and unfamiliarity with screening tools [10]. Implementation of the SBIRT model has been met with similar concerns, with providers citing lack of time and competing medical priorities in the patient interview as barriers to its use [11].

### Shared Decision Making, Self-Monitoring, and Ecological Momentary Assessment

As the fields of mental health care and substance abuse treatment have changed, there has been a greater emphasis on the importance of patient autonomy and patient involvement in treatment. Active patient participation is a critical component of recovery and enhances the personal meaning, treatment satisfaction, and quality of life for the patient [12]. Shared decision making (SDM) is an interactive collaborative process between the health care provider and the patient in which the practitioner becomes a consultant to the patient, providing information, discussing options, and supporting the patient’s autonomy as they mutually decide on treatment options [13]. SDM has been found to be associated with improved outcomes in substance-dependent patients, including increased personal control and reduced drug use [14-15].

One important component of SUD treatment and prevention that contributes to patient autonomy is the use of self-monitoring logs, in which patients are directed to record details about their alcohol and drug use, including their moods and the situations in which use occurred. This practice serves multiple purposes—it provides an opportunity for the patients to talk openly and honestly about their alcohol and drug use, it encourages patients to take responsibility for their own behavior change, and it provides information that providers can use to observe patterns and give feedback about changes in alcohol and drug use over time [16]. Ecological momentary assessment (EMA) is a method in which data are collected in real-world environments as subjects go about their lives. Assessments focus on subjects’ current state based on strategically selected moments (eg, occasions when subjects have craving). In EMA, subjects complete multiple assessments over time, providing a picture of how their experiences and behavior vary over time and across situations [17].

The self-monitoring aspect of SUD prevention and treatment lends itself perfectly to EMA, as EMA can minimize recall bias and provide a clear picture of the patterns involved in substance use [18]. Indeed, EMA has been used successfully in the field of substance use research. EMA methods have helped highlight the processes that drive drug use, cessation, and relapse and provide detailed information on mood variations and their relation to substance abuse that is not possible with other data collection methods [19]. Researchers have shown that EMA is a feasible method for collecting data from methamphetamine-dependent outpatients [20], with recovering alcoholics [21], and with cocaine users [22].

### Technological Approaches to Substance Abuse Disorder Prevention, Screening, and Treatment

In an effort to overcome some of the barriers to screening and prevention of substance use disorders, many researchers have begun to explore novel approaches using Web-based and mobile technology. These mobile technologies often focus on self-help and self-monitoring as an adjunct for traditional, face-to-face treatment in a clinician office setting and in doing so, reduce the time and cost burden on the health care provider.

While the quality of evidence is often inconsistent, there is promising research to indicate that interventions using Web-based or mobile technology for alcohol and other substance abuse can be effective [23-26]. Most recently, brief intervention applications related to substance use have focused on young adult populations and risky drinking behavior. While some studies have shown potential in reducing drinking outcomes [27-28], more research is necessary to determine overall effectiveness and whether the same strategies could be effective for substances other than alcohol. Features such as tailored feedback have shown to be more effective than similar programs without feedback [29], and interventions that combine self-administered therapy in conjunction with therapist-directed interventions show greater reductions in addictive behavior [30]. Future research is needed to determine to what extent such applications can help the primary care physician integrate SBIRT and other substance use screening models into their practice while providing significant outcomes in patient behavior.

## Methods

### Objectives

The main objective of this research will be to conduct an Office of Management and Budget (OMB)-approved randomized controlled trial (RCT) in primary care and SUD specialty service providers affiliated with Washington State University. The RCT will recruit a total of 500 SUD patients from University Health District (UHD) Clinic, a primary care clinic affiliated with the university. The patients will be randomized to receive usual SBIRT care and technology-enhanced SBIRT care. High-risk SUD patients will be referred to university-affiliated specialty providers in the area.

### Hypotheses

The RCT will address 2 primary hypotheses. Hypothesis 1 has 7 secondary hypotheses. Compared with the control group,

Significantly more intervention group patients will receive specialty SUD care within 30 days following the SBIRT encounter at the primary care clinic. The secondary hypotheses attempt to explain how and where the increased specialty care utilization occurs in the process.More intervention group patients are diagnosed with high-risk SUD.More intervention group patients are subsequently referred to specialty care at the end of the primary care clinic encounter.More intervention group patients are referred to specialty care during the 30-day following period due to failing to adhere to goals.Intervention group patients are more satisfied with the care they receive.Intervention group patients are more knowledgeable about SUD.Intervention group clinicians are more satisfied with the process.Intervention group clinicians spend less time on the SBIRT intervention and follow-up.Intervention group patients will report a greater reduction in substance use and a greater drop in Drug Abuse Screening Test (DAST-10) and Addiction Severity Index (ASI) scores within 30 days.

### Trial Process

#### Timing and Flow of the Randomized Controlled Trial

We will conduct an RCT with 500 patients with SUD risk in the UHD Clinic, a large academic primary care provider affiliated with a major public university. Recruited patients will be randomized into control and intervention arms. Both arms will take initial baseline and exit (30 days) surveys to evaluate self-reported substance use and specialty service utilization. The control arm patients will receive usual care. The intervention group patients will receive technology-enhanced SBIRT with a mobile follow-up program to track goals and substance use at home. The RCT will be managed by a team of seasoned SBIRT and addiction researchers and practitioners at the research site.

The RCT tracks participants for 30 days after the primary care encounter. We will collect feedback from the patients during the 30 days and count the number of patients who use specialty care services in specialty care programs for tobacco, alcohol, and drug abuse (both from self-reporting and from the service providers).

Since the clinical trial involves more than 9 human subjects, the RCT will be approved by the OMB as well as the university’s Institutional Review Board (IRB), which is responsible for research in the university affiliated health care providers. Figure 1 displays the flow of participants.

#### Recruitment and Consent

RCT participants will be recruited from patients visiting the UHD Clinic for their regularly scheduled primary care visit. There will be a flyer in the reception area advertising the study. If a patient expresses interest in the study, a study coordinator will come out to greet the patient and lead him or her into a separate waiting room. The study coordinator will speak with the patient and go over the eligibility criteria (see Textbox 1).

**Figure 1 figure1:**
[figure not shown]
Study flow diagram.

Eligibility criteria for study.Inclusion criteria:Aged 21 years and olderUniversity Health District Clinic patientAnswered positively to single question drug use screener: “In the past year, have you used an illegal drug (including marijuana) or used a prescription medication for nonmedical reasons?”Willing to use personal mobile device for 30-day follow-upConsents to share personal data from specialty and primary care providersExclusion criteria:In the clinic for urgent conditionsCannot read or comprehend English at 6th grade level

Once the study coordinator decides that the patient is eligible to participate in the study, they will go over the informed consent together. The informed consent is approved by both OMB and the university’s IRB. The patient will sign the form and receive a copy of the signed document. Once the patient consents, he or she becomes a study participant.

#### Randomization

The study coordinator will then use an online random number generator (randomizer.org) to randomize the participant to either the control or intervention group.

The study administrator will then search for the patient name in the SBIRT application’s admin console. The admin console searches the connected electronic medical record (EMR) records and retrieves the patient data to populate the study’s database. The patient participant’s arm will be noted in the database record.

#### Screening

In this study, we will use a standard set of screening instruments for participants in both arms. Control arm participants will be screened using paper questionnaires. Intervention arm participants will be screened using the dynamically branching iPad mobile app (see Figure 2). Although our recruitment screener only asks about drug use, we will screen for tobacco, alcohol, and drug use in this study, as many drug users have tobacco and alcohol problems that potentially need counseling or treatment. The following screening instruments will be used:

One question screeners for tobacco, e-cigarette, alcohol, and drug useMy Own Health Record questionnaire for diet, exercise, and lifestylePatient Health Questionnaire (PHQ-9) for depression screeningAlcohol Use Disorders Identification Test (AUDIT-C) questionnaire for patients positive for the 1-question alcohol screenerDAST-10 questionnaire for patients positive for the 1-question drug use screener

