#### Brief Intervention

For control arm participants, usual care will be provided. Screening scores will be manually computed and entered into the EMR by a clinician trained in SBIRT. Clinician will deliver brief intervention to participants who score moderate to high risk in any substance without technology-enhanced intervention.

For intervention arm participants, the brief intervention in the primary care office will consist of 4 steps.

Participant will be asked to rate his or her willingness to quit for all his or her at-risk substances on the iPad app.

For the substance he or she is most likely to quit, the participant completes a brief 2-part intervention using an iPad app: watching a 3-minute educational video about the substance and its risks and completing an exercise to name the pros and cons of quitting this substance (Figure 3).

When the clinician comes into the room, the participant hands the iPad over to the clinician. The clinician now has an overview of screening results, readiness to change for at-risk substances, and the participant’s personal pros and cons for the change. The clinician will conduct the brief intervention in person (Figure 4).

At the end of the brief intervention, the clinician will ask the participant to rate readiness for change again. They will work together to set up quitting or reducing use goals for at least one at-risk substance. At the end, the participant will sign on the screen and commit to the goals (Figure 5).

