#### Surveys

At the end of the primary care clinic visit, all participants will be asked to complete a survey about their experience with the process and their knowledge about SUDs. The intervention group patients will also be asked about their acceptance of the technology solution. The survey has the following components:

A 19-item validated computer system usability questionnaire is used to evaluate a computer system’s usability [33]. It also allows users to give free form answers on what he or she likes or dislikes about the system. We use it to evaluate the iPad tool in primary care clinics.A questionnaire based on the unified theory of acceptance and use of technology (UTAUT) by Venkatesh et al [34] is used to evaluate the technology solution’s ease-of-use, perceived usefulness, and the user’s social and facilitating conditions to predict the adoption of such technology solutions. The original UTAUT questions will be adapted to reflect our product.A 10-item validated patient satisfaction questionnaire will evaluate patient satisfaction with primary care providers [35].The ASI–Lite asks for drug use in the previous month, comorbid medical and mental illness, and social and legal outcomes related to drug use [36]. The ASI score is a quantitative measure of the user’s substance use.

At the end of the 30-day follow-up period, all participants will be asked to complete the screening, patient satisfaction, and ASI questionnaires again. They will also be asked to report any health care service they received during the 30 days, including any specialty SUD services. They can complete those questions on a computer or on paper. A complete schedule of all participant surveys and questionnaires is listed in Table 1.

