#### Hypotheses Testing

Since the hypotheses are primarily concerned about the observed differences between control and intervention arms, including referral rates, satisfaction level, knowledge level, and greater reduction in substance use, Student *t* tests will be used.

A chi-square test will be performed on the proportions of participants who receive specialty care to detect the significance in the difference between control and intervention arms. This test will be repeated for participants who have self-reported receiving specialty care. A chi-square test will be performed on the proportions of participants who receive specialty care referral at the end of the primary care encounter and who receive a specialty care referral during the 30-day follow-up period. For each question in the participant satisfaction survey and on the overall computed satisfaction and knowledge score, we will perform a *t* test for the answer’s mean value. Clinician interview results will be evaluated qualitatively to determine clinicians’ satisfaction with the solution.

Difference in differences regression tests will be performed on the differences in self-reported substance use amount and frequency and DAST-10 scores measured at baseline and 30 days of the study. The correlation coefficients and their confidence levels will be computed. These tests detect difference in drug use changes from control and intervention groups during the intervention period.

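### The DAST-10 baseline in the difference-in-differences for primary hypothesis 2 is taken after randomisation by iPad in one arm and on paper in the other, so a mode effect would bias that component in an unknown direction.

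*Protocol article*

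**What the plan says.** In the protocol article, the Randomization section follows consent and precedes Screening: "The study coordinator will then use an online random number generator", and the arm is then recorded in the study database. Screening comes next, and its mode depends on the arm: "Control arm participants will be screened using paper questionnaires. Intervention arm participants will be screened using the dynamically branching iPad mobile app". The DAST-10 is on the list of screening instruments, and Table 1 schedules it only at screening and at 30 days. Scoring differs too. For the control arm, the Brief Intervention section states: "Screening scores will be manually computed and entered into the EMR by a clinician trained in SBIRT". The Discussion (Summary) describes the app as an automated implementation of the measures.

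For the repeat questionnaires at day 30, the Surveys section lets every participant choose: "They can complete those questions on a computer or on paper".

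The Hypotheses Testing section fixes the analysis: "Difference in differences regression tests will be performed on the differences in self-reported substance use amount and frequency and DAST-10 scores measured at baseline" and again at 30 days. The Power Calculation section describes a different test for the same hypothesis. It takes substance use to be equal at the start and compares mean levels at day 30 only.

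**The concern.** A difference-in-differences removes an arm difference in measurement only if that difference is the same at both time points. Here the design fixes it at baseline, with all iPad in one arm and all paper in the other, and leaves it to participant choice at day 30. Randomisation does not protect against this, because the difference arises after allocation. Adjusting for baseline mode is impossible, because baseline mode and arm are the same variable.

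If patients report more on the iPad than on paper, the intervention arm starts from a higher measured score and appears to improve more with no change in drug use. If they report less, a real benefit is partly hidden. Either way, the DAST-10 result would mix the effect of the intervention with the effect of the questionnaire format. A greater DAST-10 drop is a named part of primary hypothesis 2.

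**Working it through.** **Inputs from the protocol article.** Total 500 with up to 20% attrition, so 500 × 0.8 / 2 = 200 completers per arm. Two-sided 5% test, power 0.9, medium effect, 86 per arm (Power Calculation).

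**Inputs assumed.** Medium effect means d = 0.5. The shift m (iPad minus paper) is additive, in units of the DAST-10 SD, and the SD is the same at both times. The pre-post correlation rho is 0.3, 0.5 or 0.7. The documents give none of these.

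**The plan's own figure.** The normal approximation is 2(1.960 + 1.282)² / 0.5² = 84.1, so 85 per arm. The t test gives 85.03, so 86. The stated 86 reproduces and is not in dispute.

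**Bias.** Let qI and qC be the shares answering electronically at day 30 in the intervention and control arms, and let T be the true effect.

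- Expected change, intervention: true change + m·qI − m
- Expected change, control: true change + m·qC − 0
- Difference-in-differences: T − m[1 − (qI − qC)]

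The bias is the full m when qI = qC, and half of m when qI − qC = 0.5. It is zero only if m = 0, or if at day 30 every intervention participant answers electronically and every control on paper. The plan secures neither condition.

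**False-positive rate with T = 0.** The standard error in SD units is √(2(1 − rho) × 2/200), which is 0.118, 0.100 and 0.077 for rho = 0.3, 0.5 and 0.7. The rejection probability is Φ(−1.96 + b/SE) + Φ(−1.96 − b/SE), where b is the size of the bias. It does not depend on the sign of m.

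| m (SD) | Day-30 mode mix | rho 0.3 | rho 0.5 | rho 0.7 |
|---|---|---|---|---|
| 0 | any | 0.050 | 0.050 | 0.050 |
| 0.1 | equal | 0.135 | 0.170 | 0.252 |
| 0.1 | half cancels | 0.071 | 0.079 | 0.099 |
| 0.2 | equal | 0.394 | 0.516 | 0.733 |
| 0.2 | half cancels | 0.135 | 0.170 | 0.252 |
| 0.3 | equal | 0.718 | 0.851 | 0.972 |
| 0.3 | half cancels | 0.245 | 0.323 | 0.491 |

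Example: m = 0.2, rho = 0.5, equal mix. b/SE = 0.2/0.100 = 2.0, and Φ(0.04) + Φ(−3.96) = 0.516.

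**Alternatives.** Regressing day-30 score on arm and the same baseline reduces the bias to about rho × m but does not remove it. At m = 0.2 with an equal mix, the rejection rates are 0.096, 0.211 and 0.500. A comparison of day-30 means has expectation T + m(qI − qC). It carries no baseline shift, and with one fixed mode at day 30 the second term is also zero.

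**The case against.** The strongest reply is that the documents report no mode effect at all. The rates above follow from the chosen m, and at m = 0 nothing is wrong. Participants may also tend to use at day 30 the format they met at baseline, which would cancel part of any shift. Both points stand. They make this a risk built into the design, not a demonstrated error of known size.

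Four stronger readings are tempting, and the text does not support them.

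- A reader might take the secondary hypothesis "More intervention group patients are diagnosed with high-risk SUD" as the sponsor's admission that the iPad raises DAST-10 scores. It concerns diagnoses, and screening also covers tobacco and alcohol. More diagnoses could come from the clinician's on-screen overview or a more reliable workflow, with DAST-10 answers unchanged. The direction of m stays open.
- Table 1 marks the DAST-10 as optional at screening in the intervention arm only. A reader might infer that this arm may skip it. App branching is an adequate explanation, since the instrument follows a positive drug screener and a positive drug screener is an entry criterion.
- A reader might say that the procedure breaks the equal-start assumption in the Power Calculation section. That assumption concerns substance use, not measured scores, and randomisation delivers it in expectation.
- A reader might conclude that hypothesis 2 as a whole could be declared true from an artefact. It also covers the Addiction Severity Index and self-reported use. The ASI-Lite is taken at the end of the visit in both arms with no stated mode difference, and nothing in the text lets the DAST-10 decide alone.

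**Conclusion.** The concern holds for the DAST-10 component of primary hypothesis 2. As planned, its difference-in-differences does not separate the effect of the intervention from an iPad-versus-paper shift at baseline. The bias is m[1 − (qI − qC)] in size, and the documents give neither its magnitude nor its direction. A shift of 0.2 SD would be 40% of the assumed d = 0.5. With 200 completers per arm and no true effect, it gives a false-positive rate of about 39-73% under an equal day-30 mode mix, and 14-25% if half cancels, for rho from 0.3 to 0.7. These figures illustrate sensitivity and do not predict what this trial will show. This is not detail that an article would leave to an analysis plan, because the article itself fixes the timing, the mode and the test.

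**What to change.** Give the day-30 DAST-10 in one fixed mode in both arms. Make the between-arm comparison of day-30 means the DAST-10 test, in place of the difference-in-differences on the screening score. Amend Hypotheses Testing and Power Calculation so that both name this test. The iPad screener can stay as part of the intervention.

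For participants not yet enrolled, a DAST-10 in a single mode between consent and randomisation may be added as a common baseline.

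Costs:

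- The day-30 comparison gives up the baseline information. The 86 per arm it needs is well below the roughly 200 expected, so the sample size need not change.
- Data collection is already underway. For participants past day 30 the mode cannot be fixed in retrospect, and a term m(qI − qC) remains for them. Where the mode used was recorded, report it by arm.
- The optional extra form cannot reach those already enrolled, so it would create two baseline procedures. It would also need ethics and OMB clearance. Intervention participants would answer the DAST-10 twice within one visit, which may affect their iPad answers, so equal reactivity in the two arms cannot be assumed.
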